#### Biological effects

***Secondary endpoints***

*Time to presence of asexual stage P. falciparum parasites during the six-month efficacy follow-up period* – Similar analyses as those described for the primary endpoint will be performed.

*Time to parasite density  50,000 asexual stage P falciparum parasites per microliter of blood during the six-month efficacy follow-up period* – Similar analyses as those described for the primary endpoint will be performed.

*Presence of MSP-1 3D7 parasites in clinical cases of malaria meeting the primary case definition during the six-month efficacy follow-up period* – Frequencies and percentages of cases with circulating MSP-1 3D7 parasites will be calculated by vaccine study group.

*Presence of MSP-1 3D7 parasites at a given cross-section survey time during the six-month efficacy follow-up period* – For a given survey time, the frequency and percentage of subjects with circulating MSP-1 3D7 will be calculated by vaccine study arm.

*Time to anemia defined as hemoglobin level < 8.0 g/dl during the six-month efficacy follow-up period* - Similar analyses as those performed for the primary endpoint will be conducted. In addition, a Cox model with vaccine study arm, baseline hemoglobin, and age as covariates will be applied to the data. The six-month cumulative incidence rate of anemia will be calculated for each vaccine study arm.

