This combination study of RTS,S and FMP1 demonstrated the non-interference of MSP-1 with the previously described protective effect of RTS,S. FMP1/AS02A vaccine, a blood stage vaccine, is not expected to prevent malaria infection but rather to affect the clinical disease presentation. The clinical sporozoite challenge model is not designed to, and not capable of, predicting efficacy against clinical malaria (as opposed to malaria infection); therefore, this challenge study had limited ability to detect the protective effect of FMP1. In this model, treatment is required upon detection of parasitemia, and thus Mal-019 cannot address whether FMP1/AS02A could limit parasitemia with the net effect of attenuating clinical disease. The present study will assess whether FMP1/AS02A can limit disease.

Mal-024

In 2002, following the Mal-019 challenge study, 40 participants (14 females and 26 males) were enrolled into the Mal-024 study in Kombewa, Kenya. Subjects were randomized 1:1 to receive FMP1/AS02A or *Imovax*. (Throughout the remainder of this section, we refer to the FMP1/AS02A group simply as the FMP1 group.)

Each study arm had 7 females and 13 males. The mean age  standard deviation was 33.7  9.6 years for the FMP1 arm and 32.9  11.4 years for the *Imovax* arm. All 40 participants received the first two immunizations. Three did not receive the third immunization but were followed according to the protocol. One participant who received *Imovax* was excluded from the third dose because of transient transaminase elevation; a second who had received *Imovax* missed the third immunization because of noncompliance with the visit schedule; and a third was excluded because he left the study area.

The most common side effect related to immunization was pain at the site of injection. Seventeen FMP1 and 10 *Imovax* vaccinees complained of pain at the injection site within 24 hours of immunization (p = 0.04). In most cases the pain resolved within 48 hours. There was no other difference in vaccine-related signs and symptoms.

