# JUSTIFICATION

## Malaria in Western Kenya

Malaria in western Kenya is holoendemic. Intense transmission occurs primarily by bites of the *Anopheles gambiae* mosquito. *P. falciparum* parasitemia is present in over 90% of malaria cases. *P. ovale* and *P. malariae*, which together constitute less than 10% of cases, are usually present in mixed infections with *P. falciparum.* Malaria transmission occurs all year but at a very high level during the two rainy seasons. The “long rainy season” of late March through May produces intense transmission from April through August; the “short rainy season” of October through December produces another, somewhat less intense, transmission season from November through January. The intensity of both transmission seasons can be predicted by the amount of rain seen in the preceding month and correlates with both the total population of female anopheline mosquitoes and the entomological inoculation rate (EIR, i.e., the number of infected mosquito bites per person per unit time). Cumulative malaria attack rates have been roughly 95% during the long rains and 75% during the short rains. The adult population of several villages not far from the study site has been the subject of several malaria chemotherapy and epidemiology studies. These studies typically demonstrate about 90% incidence of parasitemia over 12 weeks during a high transmission period. Approximately 25% of these infected adults will become symptomatic at some time during that period. Over the course of two disease seasons a large-scale longitudinal cohort project recently undertaken in Kisumu District (34) documented an 83% malaria parasite prevalence in the proposed study district and in the proposed study age groups (1 to 4 year-olds). The investigators of the present study conducted a longitudinal epidemiological study in 2003-2004 that indicates that monthly attack rates range from 20 to 55% in children aged 1 to 3 years in the proposed study area (unpublished data). As a conservative estimate for the purpose of calculating the sample size of this study, we have assumed that 50% of children will develop clinical malaria (as defined by the primary case definition) during the efficacy follow-up period of this study from study day 71 through study day 240. All individuals in this population are parasitemic multiple times over a lifetime. Undoubtedly, children in this population are malaria-exposed.

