### Active and Passive Case Detection of Malaria

*Active case detection* is represented by 1) the 15 scheduled MBF/CBC collections at the clinic and 2) the 13 monthly field worker home visits (see Exhibit 7 and Section 7.2), “Detailed Description of Study Stages and Visits”). All these scheduled sample collections and home visits will be undertaken whether or not children are symptomatic, and will include checks of temperature. All children known to be parasitemic with symptoms, including those with fever (≥ 37.5C) or history of fever will be documented as such and treated as medically appropriate on the same day. The malaria blood films (MBFs) of children who are afebrile and well at the clinic will be read according to a time schedule dictated by microscopist workload. Therefore, any asymptomatic, but parasitemic, children who do not have their MBFs read “in real time” will not receive antimalarial treatment. (It is anticipated that these will represent 80-90% of children during high-transmission months). During field worker visits to the subjects’ homes, any child found to be ill from any cause will be promptly transported by the field worker to the WRP KC for evaluation and appropriate medical management.

*Passive case detection* is represented by subjects’ accessibility to the 12 field stations, which are manned on a 24-hour basis by field workers, as described in Section 16.3.3. Passive case detection will be in effect from the day of screening to Study Day 0 (for all those screened), and from Study Day 0 to study end (for all those enrolled). Parents of subjects will be advised on a continuous basis to bring any ill subject to a field station for immediate transportation to the KC at any time, night or day. Field workers will have standing instructions to arrange transport to the KC for any subject with reported fever or history of fever in the past 24 hours. Thus, all such children will be evaluated with an acute MBF and CBC. Subjects will then be treated at the KC IAW Section 7.3.3 (for malaria), Section 6.3.1 (for other illnesses), clinic SOPs, and established clinic guidelines. (This facility and its staffing are described in detail in Section 7.3.)

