## Sample Size

Preliminary results from the WRAIR #1020 epidemiological study indicate that approximately 50% of children experienced at least one episode of clinical malaria in the first six months of follow-up. In this analysis, clinical malaria is defined as a parasite density  50,000 parasites per microliter in the presence of fever (axillary temperature  37.5 C). If one assumes that time to clinical malaria follows an exponential distribution, a 50% cumulative incidence rate corresponds to a hazard rate of 0.1155/month. A trial with 200 subjects per study arm, therefore, will have roughly 80% power to detect a 38% reduction in this hazard rate. A 38% reduction in the hazard rate corresponds to a 30% reduction in the six-month cumulative incidence rate. In terms of time to event, these rates imply that 25% of the subjects in the comparator group are expected to contract malaria within about 2.5 months from the third immunization; the comparable time for the FMP1/AS02A arm will be roughly 4 months. The median time to first clinical episode is expected to be 6 months and 10 months, respectively.

This sample size calculation is based on a two-sided 0.05-level logrank test. It assumes that children receive 3 doses of vaccine and then are followed for 6 months after the third dose. Cases of malaria are counted after the third dose of vaccine. Twenty percent of children are assumed to dropout during the immunization period. No further dropouts are assumed during the efficacy follow-up period.

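### Time to parasite presence, clocked from Study Day 71, would largely compare carriage at the first routine film (about Day 85) rather than time to infection

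*Protocol*

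**What the plan says.** Section 12.4.2, under Biological effects, names "Time to presence of asexual stage P. falciparum parasites during the six-month efficacy follow-up period" and gives it the same analyses as the primary endpoint. For the primary endpoint, those are a log-rank test, a Cox model with vaccine efficacy as one minus the hazard ratio, and Kaplan-Meier curves. The opening of 12.4.2 sets the origin of all six-month time-to-event analyses at SD 71. It adjusts time at risk for antimalarial use and absence only. Exhibit 8 (section 7.3.1) defines infection as any asexual density above zero. The ten-month tertiary version repeats the method and the origin.

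On who carries parasites:
- Section 4.1 cites a cohort that "documented an 83% malaria parasite prevalence in the proposed study district and in the proposed study age groups".
- Section 7.1.4 says that "any asymptomatic, but parasitemic, children who do not have their MBFs read" in real time go untreated, and expects this group to be 80-90% of children in high-transmission months.
- Section 3.5.2 says the vaccine "is not expected to prevent malaria infection but rather to affect the clinical disease presentation".

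Parasitemia is not an exclusion criterion in section 6.5, and section 7.2 schedules no parasite clearance before SD 71. The home visit near SD 71 leads to a film only after fever, history of fever or other illness. The first routine film in the efficacy follow-up period (EFP) is Visit 17, SD 85 ± 10.

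**The concern.** A time-to-event analysis of infection presumes that children are free of the event when the clock starts. Here the origin, the event definition and the method are all fixed, and together they do not meet that condition. A child who carried parasites before SD 71 is counted as an event, and the recorded time is the date of a clinic appointment.

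If most children are in that state, both curves drop steeply at one visit and the log-rank statistic is dominated by that drop. The output would still be reported as a hazard ratio, and one minus it as efficacy. Section 12.1.2 says the secondary endpoints serve to give insight into efficacy and to help choose a Phase III primary endpoint. A mislabelled measure serves neither purpose well.

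**Working it through.** **1. The plan's own figure.** Section 12.3 gives no power for this endpoint, only for the primary one: the trial "will have roughly 80% power to detect a 38% reduction in this hazard rate".
- Control hazard: ln 2 / 6 = 0.1155 per month, as stated.
- Vaccine-arm six-month incidence: 1 − 0.5^0.62 = 0.349, a relative reduction of 1 − 0.349/0.5 = 30%, as stated.
- Analysed per arm after 20% dropout: 200 × 0.8 = 160.
- Events: 160 × (0.500 + 0.349) = 135.9.
- Schoenfeld: √135.9 × |ln 0.62| / 2 − 1.96 = 0.83, giving power 79.6%.

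The stated 80% reproduces. The 160 per arm and the hazard ratio of 0.62 are carried over below; 0.62 serves only as a benchmark.

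**2. Assumptions for the parasite endpoint.**
- Carriage *p* at SD 71: 80-90%, with 50% and 0% for contrast. The documents do not give carriage on that day.
- New infection *m*: 20-55% per month. Section 4.1 gives this range as monthly attack rates in children aged 1 to 3 years; using it for new infection is an assumption.
- Films at SD 85, 115, 143, 171, 200 and 228. Carriers at SD 71 are taken to be positive at SD 85.

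**3. Share of control children with the event at SD 85.** With λ = −ln(1 − m)/30 per day, the share is p + (1 − p)(1 − e^(−14λ)). The 14-day infection probability is 0.099 for m = 20% and 0.311 for m = 55%.

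| Carriage at SD 71 | Clear at SD 71, per arm | Event at SD 85 (m = 20% to 55%) |
|---|---|---|
| 80% | 160 × 0.20 = 32 | 82% to 86% |
| 83% | 160 × 0.17 = 27 | 85% to 88% |
| 90% | 160 × 0.10 = 16 | 91% to 93% |

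For example, 0.80 + 0.20 × 0.099 = 0.82 and 0.90 + 0.10 × 0.311 = 0.93.

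**4. Power if the vaccine lowers only the hazard of new infection, by 38%.** Simulated two-sided 0.05 log-rank test over the six films, 160 per arm:

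| Carriage at SD 71, both arms | Power |
|---|---|
| 0% | about 91-98% |
| 50% | about 39-63% |
| 83% | about 15-23% |
| 80-90% | about 11-27% |

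A separate simulation used the adult rate in section 4.1 (90% parasitemia over 12 weeks, λ = ln 10 / 84 = 0.0274 per day). It gave 98%, 64% and 21% at 0%, 50% and 83% carriage, which agrees to within simulation error.

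**5. Power if carriage itself differs by arm at SD 71 (assumed differences).**
- 83% against 73%, plus hazard ratio 0.62: about 74-81%.
- 83% against 68%, no effect on new infection: about 55-63%.

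**The case against.** The tempting stronger reading is that the endpoint is wholly settled at the first film and cannot show any vaccine effect. The documents do not support it. The low power in step 4 assumes that the vaccine acts only on new infections and leaves carriage equal. Section 3.5.2 points elsewhere: the vaccine might limit parasitemia. All three doses precede SD 85, so an effect on existing infections could appear at that film, and step 5 shows that it could be detected. This part of the objection stands.

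A reader might also take 83% as the known carriage at SD 71. It comes from a separate cohort followed over two disease seasons. The 80-90% applies to high-transmission months. Provisional SD 71 is 11 April (section 16.3.1), early in the April-August season. Children with symptomatic malaria are treated throughout (sections 7.3.2 and 7.3.3), and in Mal-031 76-87% had at least one malaria episode. Carriage may therefore be lower, which is why the 50% row is shown. This stands too, but at 50% carriage power is still far below that with a clear start.

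Nor is it safe to infer that a null result would be read as no biological effect. Section 12.1.2 disclaims formal claims, and the development rule in section 4.2 rests on clinical episodes and vaccine-homologous parasitemia. Other parasite measures are also planned.

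Finally, section 12.4 leaves fuller detail to a Reporting and Analysis Plan. That could add a rule for children already positive. But the protocol does not merely stay silent: it states an origin, an event and a method which, followed as written, give a mislabelled estimate.

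**Conclusion.** The point holds in limited form. With carriage of 80-90% at SD 71 and 20-55% new infection per month, about 82-93% of control children have their event at the first routine film. The analysis is then largely a comparison of carriage at about SD 85, reported as a hazard ratio for infection. Power for a 38% lower hazard of new infection is about 11-27%, rising to 39-63% if carriage is 50%.

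It does not follow that the endpoint is blind to the vaccine, because a carriage difference built up by SD 85 could be found. The fault is in what the number means and in its weak sensitivity to new infection. It affects one exploratory secondary endpoint and its ten-month counterpart; the primary endpoint and its conclusion are untouched. The change is worth making because the better analysis needs no new data.

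**What to change.** In section 12.4.2 and the Reporting and Analysis Plan:
- Make the main analysis of parasite presence a repeated-measures comparison of parasite prevalence (for example GEE) over the scheduled EFP surveys at SD 85, 115, 143, 171, 200 and 228, by arm and survey, adjusted for age and the film taken before dose 1.
- Report log10 density alongside (for example a mixed model), stating how negative films enter. Density at scheduled collections is so far only a tertiary endpoint, listed mainly for the addendum period (section 12.1.3).
- Do the same for the ten-month version, adding the later scheduled surveys.
- If time to presence is kept, label it supportive and do not report one minus the hazard ratio as efficacy against infection.
- Do not use a clock that starts at each child's first negative film as a main analysis. A negative film after vaccination is a post-randomisation state, often following antimalarial treatment, and selecting on it breaks the randomised comparison.

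The cost is wording only, since all the films are already scheduled. The small loss is that this endpoint no longer has the same format as the primary one.

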The next logical step in the clinical development of FMP1/AS02A is to evaluate its efficacy in the pediatric population in a cautious, step-wise manner as described in this protocol. If this vaccine confers a significant delay in the onset of clinical episodes of malaria, it may be further developed either alone or with a pre-blood stage antigen as a combination vaccine, as indicated by the degree of efficacy demonstrated and by the results of a separate Phase IIb study. If the vaccine confers no reduction in clinical episodes of malaria, and there is a significant reduction in the episodes of parasitemia due to vaccine‑homologous *P. falciparum* strains, this vaccine may be developed in combination with a second MSP-1 vaccine based upon the FVO allele. If the vaccine confers no reduction in clinical episodes of malaria, and there is no reduction in the episodes of parasitemia due to vaccine‑homologous *P. falciparum* strains, the vaccine formulation will not be further developed.

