### Secondary Endpoints

Because this is a Phase IIb trial, it has many secondary endpoints. Their purpose is to gain insight into the efficacy of the vaccine and to help define a primary endpoint for a confirmatory Phase III trial. They are not intended for use to make formal claims about the vaccine.

Measurements of efficacy during the EFP:

- Times to clinical episode of *P. falciparum* malaria meeting the various secondary case definitions shown in Exhibit 8
- Time to presence of asexual stage *P. falciparum* parasites during the six-month efficacy follow-up period
- Time to parasite density  50,000 asexual stage *P. falciparum* parasites per microliter of blood during the six-month efficacy follow-up period
- Number of clinical episodes of malaria, per subject, meeting the primary case definition
- Presence of MSP-1 3D7 parasites in clinical cases of malaria meeting the primary case definition
- Presence of MSP-1 3D7 parasites at a given cross-section survey time
- Time to anemia defined as Hgb < 8.0 g/dl, whether by active or passive case detection
- Proportion of subjects with anemia (Hgb < 8.0 g/dl)

Safety during the EFP:

- Occurrences of solicited AEs during a seven‑day follow-up period (vaccination day and six subsequent days) after each vaccination (five visits: vaccination day and days 1, 2, 3, and 6)
- Occurrences of unsolicited AEs during a 30-day follow-up period after each vaccination (vaccination day and 29 subsequent days)
- Occurrences of SAEs between the first vaccination and the end of the EFP

Immunogenicity during the EFP:

- Geometric means of MSP-1 Ab titers at Visits 2, 7, 12, 17, 20, and 23 (o/a Study Days 0, 29, 57, 85, 171, and 256)

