### Laboratory Parameters

To assess effects of FMP1/AS02A vaccination on hematology and biochemistry parameters, linear mixed effects models will be applied to data on complete blood counts (CBCs), creatinine, and ALT.

Descriptive statistics for the distribution of genotypes and multiplicity of infection will be generated by vaccine study arm.

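### Section 4.2 makes a fallback development decision depend on a significant reduction in vaccine-type parasitemia episodes, but Section 12.4.2 plans only descriptive 3D7 outputs, none of which measures that

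*Protocol*

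**What the plan says.** Protocol Section 4.2 (Target Population) sets out three outcomes. A significant delay in clinical episodes may lead to further development. If clinical episodes are not reduced but "there is a significant reduction in the episodes of parasitemia due to" strains homologous to the vaccine, the product may be developed together with a second MSP-1 vaccine based on the FVO allele. If neither is reduced, "the vaccine formulation will not be further developed".

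Section 12.4.2 (Biological effects, secondary endpoints) gives two analyses of 3D7.
- In clinical cases meeting the primary definition: "Frequencies and percentages of cases with circulating" MSP-1 3D7 parasites, by vaccine group.
- At each cross-sectional survey: "the frequency and percentage of subjects with circulating MSP-1 3D7 will be calculated by vaccine study arm".

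Both are repeated for ten months as tertiary analyses. Section 12.4.5 adds: "Descriptive statistics for the distribution of genotypes and multiplicity of infection will be generated by vaccine study arm". For parasitemia of any strain, Section 12.4.2 says instead: "Similar analyses as those described for the primary endpoint will be performed". That means a log-rank test and a Cox hazard ratio with a 95% confidence interval.

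Section 12.1.2 says of the secondary endpoints: "They are not intended for use to make formal claims about the vaccine". Section 12.1.3 lists allele types per episode, infection episodes included, as a tertiary endpoint. Its heading places that endpoint in the addendum period unless stated otherwise, and the only analysis offered is the descriptive genotype summary. Section 12.4 says it describes the analyses planned for the primary and secondary endpoints and leaves fuller detail to a Reporting and Analysis Plan (RAP).

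**The concern.** The second and third outcomes in Section 4.2 turn on whether episodes of vaccine-type parasitemia were reduced, and the second requires that the reduction be significant. No endpoint counts such episodes during the efficacy follow-up period (EFP), and no 3D7 analysis compares the arms inferentially. If the trial misses its clinical endpoint, whoever applies Section 4.2 will have to choose an endpoint and a test after seeing the data, or judge from percentages.

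Section 4.2 also leaves a gap. A reduction that is present but not significant fits neither the second outcome, which needs significance, nor the third, which needs no reduction. At stake is whether an antigen is kept or dropped on a reading that nobody specified in advance.

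**Working it through.** **1. The rule beside the plan**

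| | Section 4.2 needs | 3D7 among clinical cases | 3D7 at surveys |
|---|---|---|---|
| Event | parasitemia episode of homologous type | primary-definition case carrying 3D7 | carriage on the day |
| Denominator | children at risk | cases, a group formed after randomization | children surveyed |
| Comparison | significant reduction | none stated | none stated |

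**2. The plan's own power figure**

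Inputs from Section 12.3: 200 per arm, 20% dropout before follow-up (160 evaluable), 50% control incidence at six months, hazard ratio (HR) 0.62, two-sided 0.05.
- Control hazard: ln 2 / 6 = 0.1155 per month.
- Vaccine-arm incidence: 1 − 0.5^0.62 = 0.349.
- Events: D = 160 × (0.500 + 0.349) = 135.9.
- Power (Schoenfeld): Φ(√D/2 × |ln HR| − 1.96) = Φ(5.83 × 0.478 − 1.96) = 79.6%.

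This reproduces the stated figure of roughly 80%. The protocol gives no power figure for a 3D7-specific effect.

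**3. What the percentage among cases shows**

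Let a share s of the control hazard be 3D7. The documents do not give s, so it is assumed. Over six months the cumulative hazards are a = ln 2 × s × HR(3D7) and b = ln 2 × (1 − s) × HR(other). First cases of 3D7 type number 160 × (1 − e^−(a+b)) × a/(a+b), and the 3D7 percentage among cases is a/(a+b). With s = 50%, the control arm has 80 cases, 40.0 of them 3D7.

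| Effect of vaccine | 3D7 cases, control vs vaccine | 3D7 percentage, control vs vaccine |
|---|---|---|
| HR 0.62 on 3D7 only | 40.0 vs 26.3 | 50% vs 38.3% |
| HR 1 on 3D7, HR 1.5 on other types | 40.0 vs 37.1 | 50% vs 40.0% |
| HR 0.62 on all types | 40.0 vs 27.9 | 50% vs 50% |

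The first two rows give nearly the same percentage, with a real 3D7 effect in one and none in the other. In the third row the 3D7 hazard falls by 38% and the percentage does not move. The percentage therefore does not identify a reduction in 3D7 episodes.

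**4. What the survey percentage shows**

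The denominator is sound, but the measure is prevalence. Section 7.1.4 says parasitemic children without symptoms whose films are not read in real time go untreated, and expects these to be 80–90% of children in high-transmission months. A positive survey thus does not separate a new infection from a persisting one.

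If a test were added at a single survey, with 160 per arm and a prevalence ratio of 0.62, power is Φ[(Δ − 1.96 × SE₀)/SE₁], where SE₀ is the pooled and SE₁ the unpooled standard error. For assumed control prevalence of 20%, 35% and 50% this gives 45%, 75% and 94%.

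**5. Power of a 3D7-specific time-to-event test**

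This uses the model of step 3 for clinical cases, with no effect on other types. Example at s = 50% and HR 0.62: D = 40.0 + 26.3 = 66.3, and Φ(4.07 × 0.478 − 1.96) ≈ 50%.

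| Assumed 3D7 share | Power at HR 0.62 | Power at HR 0.50 | HR detectable with 80% power |
|---|---|---|---|
| 20% | 23% | 40% | 0.29 |
| 35% | 37% | 62% | 0.41 |
| 50% | 50% | 78% | 0.49 |
| 70% | 64% | 90% | 0.55 |

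The rule concerns parasitemia, whose 3D7 rate the documents do not give. These figures are only a guide.

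**The case against.** The strongest reply is that Section 4.2 is planning text. The formal hypothesis is in Section 5.4, secondary endpoints are declared to be for insight, and naming a test for a secondary endpoint is commonly left to the RAP, which is not shown. A missing test alone would indeed be no finding. But Section 12.4.2 is not silent. It assigns primary-endpoint methods to any-strain parasitemia and percentages to 3D7, so the protocol itself fixes the weaker method for the one quantity its rule needs to be significant.

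Four stronger readings are tempting and are not supported.
- A reader might infer that 3D7 is summarized only among cases. The survey analysis uses all children surveyed.
- A reader might infer that the whole development decision rests on 3D7. The criterion applies only if clinical episodes are not reduced, and the stop outcome speaks of no reduction, without the word significant.
- A reader might infer that a uniform 38% cut would go unseen and mislead the decision. The plan also reports frequencies, and with 1:1 allocation the counts separate that case (40.0 vs 27.9) from no effect. Such a cut is also the clinical effect the trial is sized for, so the fallback criterion would not apply. What remains is that these are counts of clinical cases without person-time or inference.
- A reader might take the rise in other types in step 3 as likely. Nothing in the documents suggests it. It shows only that the percentage is not identifying.

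Section 8.3.7 also foresees several alleles in one sample, so 3D7 and other types overlap. The two-class model is a simplification.

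**Conclusion.** The point holds as a mismatch between rule and endpoints. In the branch where clinical episodes are not reduced, Section 4.2 calls for a significant reduction in homologous parasitemia episodes, and the analyses in Sections 12.4.2 and 12.4.5, followed as written, cannot supply it. The case percentage has the wrong denominator and the wrong event. The survey percentage has a usable denominator but is not an episode measure and is not compared between arms.

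The size cannot be fixed from the documents, because the 3D7 share and prevalence are not given. Under assumed shares of 20% to 70%, independent exponential hazards and 160 children per arm, a 3D7-specific test on clinical cases would have 23% to 64% power at HR 0.62. A missed effect is therefore a real possibility, and the handling of a non-significant result matters as much as the choice of test. This should be corrected, but it does not touch the primary analysis.

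**What to change.** - In Section 12.4.2 add time to first 3D7-positive parasitemia during the EFP, with all cohort children at risk and mixed infections counted as 3D7-positive, analyzed by log-rank and Cox with a 95% confidence interval. State how carriage already present at Study Day 71 is handled.
- Support it with a repeated-measures model (for example GEE) of 3D7 positivity by arm over the scheduled EFP visits, and report 3D7-specific clinical episodes per child at risk as secondary.
- In Section 4.2 say which of these results triggers the rule and how a non-significant reduction is read. Report the interval, and do not treat non-significance as no reduction. The alternative is to remove the word significant from that rule.

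The cost is wording and some programming before the partial unblinding at Study Day 240. Exhibit 7 already schedules 3D7 allotyping at the six EFP clinic visits (Days 85, 115, 143, 171, 200 and 228) and for febrile children found at home visits. For children who present themselves when sick, Sections 7.1.4 and 7.3.2 name only the blood film and blood count. The protocol should state that these samples are allotyped too, as its existing endpoint on 3D7 in clinical cases already presupposes. The drawback is possibly limited power, as shown above.
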